### Intervention description

The NAT counselling intervention programme begins with an initial screening using the 15-item version of the Refugee Health Screener [123, 124]; to assess trauma exposure and symptom severity in adult refugees. Based on their RHS scores, participants are allocated into three groups: low (RHS ≤ 12; green), moderate (RHS 13–36; yellow) and high (RHS ≥ 37; red) severity of trauma reaction; high levels indicate clinical relevance (Table 2).

**Table 2 Tab2:** Allocation according to assessed trauma exposure and trauma reactions, taking into account safeguarding procedures

**No to low stress (RHS ≤12)**
Individuals in this category exhibit low trauma-, depression-, and anxiety reaction and good resilience. They are expected to adapt well and effectively cope with the challenges of daily life in Germany.
**Moderate stress (RHS 13–36 or no acute danger to self or others)**
Individuals in this category are unlikely to meet diagnostic criteria for trauma related disorders but are expected to have experienced trauma exposure. To protect these individuals from developing a trauma related disorder in the future, NAT counsellors will continue to provide step 2, 3 and 4 of NAT. In NAT, the counsellor guides the client in creating a chronological narrative of their life, focusing on traumatic experiences while also incorporating significant positive life events. This process allows clients to contextualise their network of sensory, cognitive, and affective memories of the past, thereby addressing the trauma memory structures. Moreover, NAT enables clients to reflect on their entire life journey, fostering a sense of personal identity and agency in the present ‘here and now’ and a positive projection of the client’s individual future. This approach conveys a notion of integration and a sense of achievement regarding their life in Germany. Implementing peer counsellors at this point leverages the ability to learn from role models while reducing cultural barriers such as language or varying interaction styles. Licensed psychotherapists and experts in psychotraumatology supervise the process, ensuring the correct application of the NAT intervention. In the event of worsening symptoms, a referral is being discussed based on a carefully developed protocol and set of criteria.

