The overarching objective of this project is to pick up the key elements of this extensive knowledge gained from diverse countries of origin of refugees and integrate these into the German mental health system. To this end, we introduce a stepped-care trauma rehabilitation programme [121, 122] expanding the system with a peer counsellor component called *‘NAT counselling intervention’*, which integrates a screen-to-counsel approach for refugees residing in temporary accommodation in Germany (see Fig. 2). The specific goals of the ‘NAT counselling intervention’ are: (1) to invite asylum seekers to participate in a screening session conducted by a trained and assigned peer NAT counsellor with a similar cultural background, to assess potential psychological sequelae of traumatic events; the results of the screening are evaluated, and the client is categorized based on the logic of a traffic light system: red, yellow, or green and then referred to appropriate help, based on the severity of score identified by the 15-item Refugee Health Screener [123], a validated tool with excellent psychometric properties to screen for trauma related symptoms and probable diagnoses [124]; (2a) to deliver a specific counselling intervention called *‘NAT Narrative Trauma Work’* [125], adapted from NET and delivered by counsellors, for refugees with subclinical levels of symptoms (‘yellow’ group; RHS score of 13–36); and (2b) to facilitate the referral of refugees with a high likelihood of trauma related disorders (‘red’ group’; RHS score of ≥ 37) to a licensed psychotherapist^1^ for appropriate treatment, or (2c) to monitor and reevaluate cases with low symptoms; (3) follow-up; and (4) monitor psychological resources that enable individuals to participate in the community and society (‘well-being monitor’).

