### Eligibility criteria

*Refugees.* All adult asylum seekers (≥18 years) living in or arriving at the collaborating initial intake facilities are eligible to participate in the study and are offered NAT step 1, the screening interview with RHS-15 including feedback and referral if needed. Exclusion criteria include: severe cognitive impairment or communication problems that prevent participation in interviews, as well as individuals with severe intellectual or psychiatric disabilities who would qualify for guardianship (legal/ethical considerations).

For NAT steps 2 (checklist intake), 3 (lifeline laying) and 4 (narrative event-telling sessions), participants with an RHS score (items 1–13) between 13 and 36 points (‘yellow group’) are eligible; exclusion and referral to specialist care will occur in the case of acute psychiatric illness, acute suicidal ideation or danger to others, as well as acute and persistent intoxication that would prevent effective NAT sessions.

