**Severe stress (RHS ≥ 37 or acute danger to self or others)**
Individuals in this category likely meet the diagnostic criteria for a mental health disorder or present an immediate danger to themselves or others. In such cases, individuals are referred to a licensed psychotherapist for clinical assessment and guideline-based treatment. Referrals are made to various service providers, including psychosocial centres, collaborating private practitioners, licenced psycho-therapists, outpatient clinics and hospitals. In cases of immediate danger to self or others, referrals for inpatient treatment may be necessary and directed to specialised clinical services in the region (psychiatric hospitals, acute care units, or, when appropriate, law enforcement).

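### The moderate (NAT) heading in Table 2 joins score and danger status with 'or', so it overlaps both other rows and contradicts the allocation rule stated elsewhere

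*Protocol article*

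**What the plan says.** Table 2 (Intervention description) is captioned as the allocation table and is said to take safeguarding into account. Its three row headings are:

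- Low: "No to low stress (RHS ≤12", with no condition on danger.
- Moderate, the row that continues to NAT steps 2–4: "Moderate stress (RHS 13–36 or no acute danger to self or others".
- Severe, the row referred to a licensed psychotherapist: "Severe stress (RHS ≥ 37 or acute danger to self or others".

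Other sections state the rule differently:

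- The sentence introducing Table 2 gives three separate score bands: "low (RHS ≤ 12; green), moderate (RHS 13–36; yellow) and high (RHS ≥ 37; red) severity of trauma reaction".
- Eligibility criteria makes the score range the condition for NAT steps 2–4: "participants with an RHS score (items 1–13) between 13 and 36 points (‘yellow group’) are eligible". It then adds: "exclusion and referral to specialist care will occur in the case of acute psychiatric illness, acute suicidal ideation or danger to others".
- The programme goals, at the end of the background section on treatment approaches, give the yellow band as 13–36 and describe goal 2b as "to facilitate the referral of refugees with a high likelihood of trauma related disorders (‘red’ group’; RHS score of ≥ 37".
- Criteria for discontinuing or modifying allocated interventions re-assigns a client to the red group in the event of danger to self or others.
- Implementation, under Assignment of interventions: allocation, bases the regression discontinuity design (RDD) on the RHS-15 sum of items 1–13 with thresholds at 13 and 36. It adopts the fuzzy version because some clients scoring in the yellow range have to go to the red group.

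**The concern.** An allocation table should place each client in one row. Joined by 'or', the moderate heading is met by the score alone or by the absence of danger alone. A client with RHS 45 and no acute danger then fits both the NAT row and the psychotherapy row. A client with RHS 20 in acute danger fits the same two rows. A client with RHS 5 and no danger fits both the low row and the NAT row.

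Two things would be at stake if the table were followed as printed. The first is safeguarding: a mid-range score would satisfy the NAT row despite acute danger, and a score of 37 or more without danger would also satisfy it, although other sections send both clients to specialist care. The second is the RDD, which needs assignment to change at the cutoff. The only departure from the cutoffs that Implementation describes runs from yellow to red. The printed heading would also permit red to yellow and green to yellow.

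**Working it through.** The plan gives no figure to reproduce. The check is an enumeration of the printed rule.

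**Inputs.** The sum of items 1–13 runs from 0 to 52 (Assessment (refugees)), which is 53 scores: 13 in 0–12, 24 in 13–36 and 16 in 37–52. Acute danger is yes or no. That gives 53 × 2 = 106 combinations.

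**Rule as printed in Table 2.** Low if score ≤ 12. Moderate if score is 13–36 OR there is no danger. Severe if score ≥ 37 OR there is danger.

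| Score | Danger | Rows met | Combinations |
|---|---|---|---|
| 0–12 | no | low and moderate | 13 |
| 0–12 | yes | low and severe | 13 |
| 13–36 | no | moderate only | 24 |
| 13–36 | yes | moderate and severe | 24 |
| 37–52 | no | moderate and severe | 16 |
| 37–52 | yes | severe only | 16 |

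Two rows met: 13 + 13 + 24 + 16 = 66 of 106. One row met: 24 + 16 = 40. No combination meets none.

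**Source of the overlaps.** The moderate heading is involved in 13 + 24 + 16 = 53 of the 66. The other 13 (score 0–12 with danger) arise because the low heading has no danger condition while the severe heading takes danger at any score. As an arithmetic comparison only, and not as a proposed rule, joining the two conditions of the moderate heading with 'and' removes the 53 and leaves these 13. Changing one word would therefore not make the table unambiguous.

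**Rule as stated elsewhere.** Under the bands in Eligibility criteria and Intervention description, and the thresholds in Implementation, each of the 53 scores falls in one group. Of the 16 scores from 37 to 52 without danger, none is ambiguous. For a score of 13–36 with danger, Eligibility criteria and Implementation both direct the client away from NAT. For a score of 0–12 with danger, the bands alone point to the low group, whereas the severe heading and the discontinuation section point to the red group. Table 2 does not say which heading takes precedence.

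These counts are combinations, not clients. The documents give no distribution of scores or of acute danger, so 66 of 106 is not an expected share of participants.

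**The case against.** The strongest reply is that this is a slip in one heading. The score bands agree across the programme goals, Eligibility criteria, Table 1 with its note, and the sentence introducing Table 2, and the Implementation thresholds match them. The text within the rows also resists the literal reading: the moderate row describes people unlikely to meet diagnostic criteria, and the severe row describes people who likely do and says that they are referred. Taken literally, the heading would also make every low-score client without danger eligible for NAT, at odds with the watchful-waiting group in Table 1. Danger in the yellow range is dealt with in three other sections. All of this stands, and it makes a drafting error the likely explanation.

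It does not remove the contradiction. Table 2 is the only place where score and danger status are combined into group labels, and it is presented as the allocation table.

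A reader might infer more: that the RDD rule is broken, that counsellors may choose between NAT and referral for most red clients, or that the discontinuities at 12/13 and 36/37 vanish. The documents do not support this. Implementation states the assignment rule itself and does not cite Table 2. Its only link to the table is indirect, through the stepped-care model that the table summarises. No section gives counsellors discretion over clients scoring 37 or more, and nothing shows that any site uses the heading literally. Counsellors do conduct the baseline interview and deliver NAT, and no one is blinded, so an ambiguous label could open a route to selective assignment. That remains a possibility, not a finding.

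**Conclusion.** The moderate heading in Table 2 is wrong as written: it overlaps both neighbouring rows and contradicts the score bands and the danger provisions stated elsewhere in the protocol. A second, smaller overlap (RHS 12 or less with acute danger) lies between the low and severe headings. Together they leave 66 of 106 combinations of score and danger in two rows.

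This is an inconsistency in a stated allocation and safeguarding rule, not a failure of the design. Consequences for assignment at the cutoffs, or for safeguarding, follow only on the assumption that sites apply the Table 2 headings as printed, and the documents give no evidence for or against that. The counts assume that 'or' is read inclusively and that danger is recorded as present or absent.

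**What to change.** Reconcile the three Table 2 headings with the programme goals, Eligibility criteria, the sentence introducing the table, the text of the severe row, the discontinuation section and Implementation. After the revision, every combination of score and danger status should map to exactly one group. The table should state whether score and danger status must hold jointly and which takes precedence, including for low scores with acute danger. Which clinical rule applies is for the sponsor to confirm.

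Then check that any form or manual that counsellors use for allocation follows the same logic. First recruitment was planned for April 2024 and the protocol version is dated December 2024, so it is also worth confirming that no client already screened was allocated under the printed headings. If any was, the departure should be recorded and taken into account in the fuzzy RDD.

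The cost is a wording change in one table and a short check of field materials. Sample size, outcomes and analysis are unaffected.

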**Severe stress (RHS ≥ 37 or acute danger to self or others)**
Individuals in this category likely meet the diagnostic criteria for a mental health disorder or present an immediate danger to themselves or others. In such cases, individuals are referred to a licensed psychotherapist for clinical assessment and guideline-based treatment. Referrals are made to various service providers, including psychosocial centres, collaborating private practitioners, licenced psycho-therapists, outpatient clinics and hospitals. In cases of immediate danger to self or others, referrals for inpatient treatment may be necessary and directed to specialised clinical services in the region (psychiatric hospitals, acute care units, or, when appropriate, law enforcement).

### Criteria for discontinuing or modifying allocated interventions

In the event of danger to self or others, deterioration of trauma reactions or signs of other (comorbid) psychological symptoms, the client will be re-assigned to the red group and receive psychotherapeutic service or treatment at an acute care facility within the German health system. Thereafter, treatment delivery will follow the principles of the red group in full extent.

### Strategies to improve adherence to interventions

Counsellors will be provided with extensive supervision. Moreover, after conclusion of NAT, the counsellors will fill out a questionnaire asking for adherence to key principles of the NAT procedure for the specific client.

### Relevant concomitant care permitted or prohibited during the trial

All concomitant care that targets other than trauma related symptoms will be permitted.

### Provisions for post-trial care

Post-trial care will follow the regular public health system services.

### Outcomes

Outcomes of interest include the participants´ somatic and psychological symptoms, social integration, mental health literacy of the client, general life satisfaction, and post-migration stressors. Baseline and a follow-up assessment will be administered by NAT counsellors in face-to-face interviews and will assess psychological symptoms and social integration. Additional instruments are listed in Table 3 will be administered online.

**Table 3 Tab3:** List of instruments of the well-being monitor

Outcome	Measure	Author	Admin.
Somatic symptoms	Somatic Symptom Scale-8 (SSS8)	Gierk et al. [129]	online
Psychological symptoms	Refugee Health Screener (RHS-15)	Hollifield et al. [130]	both
Life satisfaction	Satisfaction with Life Scale (SWLS)	Diener et al. [131]	online
Social networks	Lubben Social Network Scale (LSNS-6)	Lubben [132]	online
Social and economic integration	Immigration Policy Lab Integration Index (IPL-12)	Harder et al. [133]	both
Mental Health literacy Scale	Mental Health Literacy Scale (MHLS)	O’Connor et al. [134]	online
Resilience	Brief Resilience Scale (BRS)	Smith et al. [135]	online
Self-efficacy	General Self-Efficacy Short Scale-3 (GSE-3)	Doll et al. [136]	online
Food insecurity	Food Insecurity Experience Scale (FIES)	Cafiero et al. [137]	online
Food environment	Access to preferred food types	Adapted from Hadley et al. [138]	online
Aggression	Adapted version of the event scale of the appetitive aggression scale	Weierstall et al. [139]	both
Note: Both = to face-to-face interviews and online			

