### Recruitment

Social workers on site inform refugees in collaborating initial intake facilities and hand out flyers about the programme, including participation instructions. Additionally, NAT counsellors will be present in the facilities on a regular basis. With it, refugees who would like to participate can request to register for participation. Moreover, with bi-monthly visits at the initial intake facilities, public health experts and research assistants will invite refugees to participate in the online self-assessments of the Well-being Monitor.

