#### Assessment (refugees)

Data collection from refugees begins with a face-to-face interview conducted by one of the NAT counsellors (see Sect. Intervention description) and continues with 10-minute monthly online assessments (Well-being Monitor). Approximately 6 to 9 months after the initial screening, refugees will be invited to a face-to-face follow-up interview.

At the start of the face-to-face baseline interview, we will ask for demographic information, screen for trauma related symptoms, and collect information on social and economic integration. The follow-up interview after 6–9 months will re-assess levels of psychological distress and integration.

The 15-item Refugee Health Screener [123] will be used to assess the severity of trauma related reactions. The RHS was adapted from validated instruments for depression, anxiety and PTSD to screen for trauma related reactions in refugee populations. Each item is rated on a scale from 0 (not applicable at all) to 4 (extremely) and a total score of items 1–13 indicates the severity of symptoms (0–52) and the intensity of treatment required. Items ask for instance for nightmares, loss of interest or other trauma related symptoms. Items 14 and 15 are taken into account in a qualitative way. The RHS was recently validated with refugees in the German context [124]. Kaltenbach et al. [124] found high sensitivity and good feasibility, reliability and validity for both the self-rating and interview versions. Strong psychometric properties of the RHS were also found in other studies in Germany [147, 148] and elsewhere [149, 150].

An adapted version of the Appetitive Aggression Scale [139] for refugees will be used to assess aggression. The AAS is a 15 item semi structured interview that measures appetitive aggression according to the extent of agreement to statements, on a scale ranging from 0 (disagree) to 4 (agree) for each item. A total sum score will be used to measure severity of aggression (max 60).

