[3] To assess the effectiveness of NAT compared to the comparison groups (see Tables 1 and 4), we will combine the figures resulting from RDD with traditional approaches (GLM, clinical significance). In the RDD, we will calculate a local average treatment effect (LATE) of the intervention on primary (RHS-15) and secondary (LSNS, BRS, SWLS, SSS8) outcomes (see Table 1). To this end, we will firstly test whether the main criteria for a valid RDD are held. Using a graphical method (scatterplot), we will examine the relationship between the eligibility (RHS at baseline) and outcome (follow-up) variables. We expect the RHS score to be discontinuous at the cutoff values. In contrast, we do not expect to see discontinuities in relevant covariates at the cutoff, which would violate the assumptions of an RDD. Next, separate regression lines will be fit on both sides of a cutoff value using an ordinary least squares (OLS) regression as the starting point. Alternative functional forms will be tested with the goal of ensuring an unbiased estimation. The LATE will be computed directly as the difference between the regression lines at the cut-off (intercept). To test the statistical significance of the difference between the two conditions, we will use a *t*-statistic, dividing the treatment effect (difference between regression lines at cut-off) by the sum of the square of the standard errors of the comparison group (*SE*_*comparison*_) and the intervention group (*SE*_*interventio*n_). The calculated *t*-statistic will then be compared to a critical value from the *t*-distribution for the given degrees of freedom (*DF*). The degrees of freedom will be determined based on the number of the observations and the parameters estimated in the two separate regressions. In the most simple form, *DF = n*_*comparison*_
*+ n*_*intervention*_
*- 4*. The test will be two-sided. Moreover, we will run falsification tests and sensitivity analysis to ascertain the validity of the RDD [178], examine whether results are sensitive to the choice of bandwidth [144], run placebo tests on exogenous covariates and on the outcome at values other than the actual cutoffs [145]. Prespecified subgroup analyses will explore potential heterogeneity in treatment effects across different demographic and clinical characteristics. Adjusted analyses will account for potential confounding factors identified a priori.

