Generalised linear mixed models (GLMM) with subgroups defined by the RDD will be used in addition and allow for integration of multiple follow-ups, if robust (*N*_min_ is sufficient to detect a small to moderate effect). Thus, to test the efficacy of NAT in comparison to our controls in regards to primary and secondary outcomes, we plan to use separate generalised linear mixed models (GLMMs) in R. To account for non-independence of measurements, we will include individuals as a random part of the models. To account for repeated measures, we will control the within-group variance for the effect of time, i.e. baseline and 3 and 6-month follow-ups, according to A Field, Z Field and J Miles [179]. To estimate the significance of the fixed terms, we plan to fit the models using maximum likelihood (ML), and compare models with and without each fixed term using likelihood-ratio tests [180]. In cases where the interaction term is significant, we will use post hoc Tukey tests using the R package emmeans [181] to assess which contrasts differ significantly. To correct for multiple comparisons controlling the false discovery rate, we will further adjust P-values accordingly [182].

Additionally, effect sizes will be estimated by calculating Cohen’s d [183] for within and between group differences following W Lenhard and A Lenhard [184]. Clinically significant change will be calculated using the reliable change index, following NS Jacobson, LJ Roberts, SB Berns and JB McGlinchey [185].

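### No pre-NAT value is secured for the online-only secondary outcomes, yet the mixed models for them start from a baseline

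*Protocol article*

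**What the plan says.** The section on statistical methods for primary and secondary outcomes names the outcomes for the effectiveness question: "primary (RHS-15) and secondary (LSNS, BRS, SWLS, SSS8) outcomes". It then plans mixed models for primary and secondary outcomes alike, with time entered as "i.e. baseline and 3 and 6-month follow-ups".

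The Outcomes section says the face-to-face baseline and follow-up interviews "will assess psychological symptoms and social integration". Of everything else it says: "Additional instruments are listed in Table 3 will be administered online". In Table 3, SSS8, SWLS, LSNS and BRS are all marked online. Only RHS-15, IPL-12 and the aggression scale carry the entry defined as "Note: Both = to face-to-face interviews and online".

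Assessment (refugees) describes the baseline interview in the same way: "we will ask for demographic information, screen for trauma related symptoms, and collect information on social and economic integration". Data collection then "continues with 10-minute monthly online assessments (Well-being Monitor").

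The consent section requires separate consent for the monitor and opens it to everyone, whether or not they qualify for NAT. The Recruitment section describes how people enter it: "with bi-monthly visits at the initial intake facilities, public health experts and research assistants will invite refugees". No passage of text dates the first monitor relative to screening or to the first NAT session.

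**The concern.** The analysis needs a starting value for each secondary scale, and the described baseline visit does not collect one. The first value of SSS8, SWLS and BRS comes from whichever monitor a client happens to complete first. When that happens depends on a separate invitation and consent, not on NAT.

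This would not be neutral between groups. Table 1 compares NAT with clients awaiting NAT. A waiting client's first monitor precedes NAT by definition. A prompt starter's first monitor may come during NAT or after it. What the model calls baseline would then depend on treatment timing, and any effect already present at the first monitor would be removed from the change of NAT clients but not from that of the controls.

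Objective 3 includes integration and overall well-being, which these scales serve. A pre-treatment value that was never collected cannot be recovered by later analysis text.

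**Working it through.** The plan states no figure on this point, so the check is a side-by-side reading followed by an illustration.

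**1. Which scales have a face-to-face baseline?**
- RHS-15: yes (Table 3, marked for both modes; described in the baseline interview).
- SSS8, SWLS, BRS: no (Table 3, online; absent from the described interview).
- LSNS: online in Table 3. However, Assessment (refugees) introduces it as the measure of social integration, and the Outcomes section says the interviews assess social integration. IPL-12, marked for both modes, could be what is meant there. The status of LSNS is unclear.

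**2. When does the first online value arise?** Data collection begins with the interview and continues with the monitor. Entry is by invitation at bi-monthly visits, which can mean twice a month or every two months. The gap from screening to first monitor is not fixed, and neither is the gap from screening to NAT.

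**3. What do the models use?** Baseline, 3 months and 6 months. The monthly monitor can supply the 3- and 6-month values. Nothing in the text assigns it the baseline value.

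**4. Two clients followed as written.**
- Client A is screened, starts NAT promptly and then completes a first monitor. The first SWLS, BRS and SSS8 values are taken under or after treatment.
- Client B is screened, waits for NAT and completes a first monitor while waiting. The first values are taken before treatment.

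Both first values could enter the same model as baseline.

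**5. What this does to a change contrast.** Let *d* be the true standardised effect, *p* the share of NAT clients whose first monitor comes after NAT has begun, and *f* the mean share of the effect already present in them. The expected change contrast is *d*(1 − *pf*). None of the three values is in the protocol. Taking *d* = 0.5 and *p* = 1 as assumptions, with *n* per group = 2(1.960 + 0.842)²/contrast² (SD 1, two-sided 5%, 80% power):

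| *f* | contrast | *n* per group |
|---|---|---|
| 0 | 0.50 | 63 |
| 0.25 | 0.375 | 112 |
| 0.50 | 0.25 | 252 |
| 0.75 | 0.125 | 1,005 |

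With *p* = 0 there is no loss, whatever *f* is. The table shows how the mechanism works; it does not estimate what will happen in this study. It also assumes that the NAT effect builds up in one direction.

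**6. The regression discontinuity analysis.** Its running variable is baseline RHS and its dependent variable is the follow-up outcome. The local effect is the gap between two regression lines at the cutoff, which needs no baseline value of the secondary outcome. Without one, the analysis loses a covariate for precision and a placebo variable that should show no jump at the cutoff. Placebo tests on exogenous covariates can still use the demographics from the interview.

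**The case against.** The strongest reply is that this is a point about absence, and the Participant timeline figure, which might place a first monitor at baseline, is not shown. That limits the point to what the printed text secures. It does not remove it, because the text on consent, recruitment and assessment still links entry to the monitor with invitations and not with the start of NAT.

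A reader might infer that these scales have no measurement before NAT at all. The protocol does not support that. Everyone is invited to the monitor, clients awaiting NAT are a named comparator, and some first monitors will precede NAT. The Recruitment text does not make screening a condition for the invitation either.

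A reader might also infer that the regression discontinuity results, the before/after comparison or the reliable change results fail. The first does not follow, for the reason given in step 6. On the other two, the before/after comparator is described in terms of symptom trajectories, for which RHS-15 has a face-to-face baseline. The text does not say that reliable change will be calculated for the four secondary scales.

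Finally, the mixed models are additional to the regression discontinuity analysis and conditional on adequate numbers. This lowers the weight of the point. It does not make the baseline in those models any better defined.

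**Conclusion.** The point holds as a mismatch between assessment schedule and analysis. In the printed text, SSS8, SWLS and BRS, and LSNS if Table 3 governs, are collected only in an online monitor that follows screening and is not tied to the start of NAT. The mixed models still take baseline as the first time point for the secondary outcomes. For prompt NAT starters that value may fall during or after NAT; for waiting clients it falls before. Change could therefore be understated in NAT clients.

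The size cannot be derived. It depends on how many clients start NAT before their first monitor and on how much of the effect is present by then, and the protocol gives neither. The direction assumes that NAT helps and that the benefit builds up steadily. The primary outcome and the regression discontinuity estimate stand.

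The change should be made, because it is cheap and a missed pre-treatment value cannot be collected afterwards.

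**What to change.** 1. State when the first Well-being Monitor is completed relative to the first NAT session. Have it done on the existing tablets at the screening visit, or at the latest before NAT step 2, with its consent taken at that time.
2. In the secondary-outcome models, accept as baseline only a monitor dated before the first NAT session. Do not enter a later first monitor as baseline. Analyse clients without a pre-NAT monitor by follow-up level and not by change, and report how many there are in each group.
3. Say whether LSNS belongs to the face-to-face interview or only to the monitor, so that Table 3 and the description of the scale agree.

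The cost is about 10 more minutes at first contact, which is the stated length of one monitor, plus a sentence or two of analysis text. Analysing by follow-up level gives up adjustment for the starting value, so it should remain the fallback.
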